### Objectives

A randomised controlled blind study is planned to objectively evaluate the efficacy of modified ultrasonic scalpel haemorrhoidectomy in the treatment of haemorrhoids. The healing time of the incision, the time taken for patients to return to normal activities, postoperative complications, evaluations of anal function 3 months and half a year after surgery, an evaluation of the quality of life at half a year after surgery, and an evaluation of the patients’ satisfaction rates half a year after surgery will be measured.

To assess safety, the incidence of adverse events (AEs) and serious adverse events (SAEs) between the two study groups will be compared to show the potential risks for patients.

### Design

#### Setting

This will be a randomised, single-blind, parallel controlled study. Patients who meet the inclusion criteria will be divided into a treatment group and a control group, each with 39 patients. The treatment group will undergo modified ultrasonic scalpel haemorrhoidectomy, and the control group will undergo a Milligan-Morgan operation. The study will be conducted at Shangjin Hospital of West China Hospital of Sichuan University.

#### Participants

Eligible participants who meet the diagnostic criteria for haemorrhoids in the Clinical Diagnosis and Treatment Guidelines for Hemorrhoids (2006 edition), formulated by the Colorectal and Anal Surgery Group of the Chinese Medical Association Surgery Branch and the Anorectal Branch of the Chinese Society of Traditional Chinese Medicine, will be enrolled. All the participants will have been treated and hospitalised by the Department of Integrated Traditional Chinese and Western Medicine of West China Hospital of Sichuan University.

The trial has been approved by the Ethics Committee on Biomedical Research at West China Hospital of Sichuan University (Approval code: NO. 2020–367). It is also registered in the Chinese Clinical Trial Registry (Registration ID: ChiCTR2100047229).

Inclusion criteria.Patients with the clinical manifestation of mixed haemorrhoids with symptoms of internal haemorrhoids and external haemorrhoids existing at the same time. Among them, internal haemorrhoids should manifest as stage III (grade) or higher;Patients aged 20–70 years without obvious surgical contraindications;Patients who provide informed consent, with good compliance, and are able to cooperate to complete all clinical research content.

Exclusion criteria.Patients with haemorrhoids combined with anusitis;Patients with haemorrhoids combined with inflammatory bowel disease;Patients with suppurative infection around the anorectal canal;Patients with intestinal infectious diseases (e.g. dysentery);Patients diagnosed with outlet obstructive constipation.

Withdrawal criteria.Patients who exhibit poor compliance during the study, which can affect the effectiveness evaluation;Patients who have serious adverse events, complications and special physiological changes and are not able to continue the experiment;Patients who quit on their own volition during the study;Patients who withdraw from the trial, are lost to follow-up, or die due to various other reasons;Patients who have incomplete data that affect the validity judgement.

#### Additional consent provisions for the collection and use of participant data and biological specimens

On the consent form, participants will be asked if they agree to use of their data should they choose to withdraw from the trial. Participants will also be asked for permission for the research team to share relevant data with people from the Universities taking part in the research or from regulatory authorities, where relevant.

This trial does not involve collecting biological specimens for storage.

#### Recruitment and trial timeline

Researchers will recruit participants from the inpatient wards of the Department of Integrated Traditional Chinese and Western Medicine. After screening patients who meet the inclusion and exclusion criteria, the researcher will inform the participants of the different treatment methods available for their condition, provide information about the study, and have the participants sign a written informed consent form. A copy will be kept by the participant, and the original will be kept at the hospital. Considering the admission to haemorrhoid surgery in our hospital and the experience of the last 2 years, it is feasible to recruit the calculated patient sample size. Other strategies to increase recruitment include announcing the study on our hospital website and providing information in the waiting room of the hospital.

The participants who meet the criteria will be registered, their baseline data and clinical features will be collected before the operation, and measurements will be taken at each observation time node according to the CRF form after the operation (Table 1). Participants who met the withdrawal criteria shall strictly follow the criteria and provide records. The registration process, the intervention and evaluation schedule, and the study flow chart are shown in Table 1 and Fig. 1.

**Table 1 Tab1:** Schedule of the registration process, the intervention, and evaluations

Measures	Preoperative	Daily in-hospital study visits								Follow-up					
		POD 0	POD 1	POD 2	POD 3	POD 4	POD 5		POD ≥ 6	W 2		W 3	W 4	M 3	M 6
Incision healing time										X	X		X		
Recovery time										X	X		X		
Pain VAS		X	X	X	X	X	X	X		X	X		X		
Urinary retention		X	X	X	X	X	X	X							
Postoperative bleeding		X	X	X	X	X	X	X		X	X		X		
Postoperative oedema		X	X	X	X	X	X	X		X	X		X		
Anal stenosis	X	X	X	X	X	X	X	X		X	X		X	X	X
Cleveland incontinence score	X	X												X	X
SF-36	X	X													X
Satisfaction survey		X													X
Adverese events		X	X	X	X	X	X	X		X	X		X	X	X

*POD* Postoperative day, *W* Week, *M* Month, *VAS* Visual analogue score, *SF36* 36-Item short form health survey

**Fig. 1 Fig1:**
[figure not shown]
Flow chart of the research phases. VAS, visual analogue scale; SF-36, 36-Item Short Form Health Survey

#### Sample size

This study is a randomised controlled trial to evaluate modified ultrasound scalpel haemorrhoidectomy versus the Milligan-Morgan operation for mixed haemorrhoids. According to previous studies [19], the mean value of the experimental group is 10.50, the mean value of the control group is 13.40, and the standard deviation is 3.46 and 3.66, respectively. Two-sided tests is needed, with a test level of 0.05. Using the PASS 15.0 software, the sample size of the two groups is 33, and according to the 15% loss of follow-up, 78 subjects will be expected to be finally collected.

#### Randomisation and blinding

Participants will be randomly assigned equally to the two study groups with the use of simple randomisation, in which a third-party statistician will use computer software to generate pseudorandom numbers. Only the clinical data manager will have access to the random number table in the computer. Subjects will be enrolled by a research assistant in the order of enrolment time. Allocation will be made by the clinical data manager using the random number table. The statistician will be blinded to the allocation of subjects during the statistical analysis.

Since the surgical operator and the observer must know which group each subject has been assigned to, they cannot be blinded. The study has a single-blind design in which the investigators will be aware of the surgical procedures used in the different trial groups, but the participants will be unaware of them.

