#### Secondary efficacy assessments

The statistical description and inference of the secondary indicators will be based on the characteristics of the data, and the appropriate descriptive indicators and hypothesis testing methods will be selected.

The comparison of general conditions between the two groups will be analysed by appropriate methods according to the type of indicators. The comparison between the groups of measurement data will be compared by the *t* test (homogeneity of variance, normal distribution) or the Wilcoxon rank sum test according to the distribution of data, and the chi-square test or exact probability method (if the chi-square test is not applicable) will be used for count data. The Wilcoxon rank sum test or stratified chi-square test (CMH test) will used for ranked data. Data analyses will be performed by statisticians who are independent of the study team and who are blinded to the group assignments. The acceptable significance level for all analyses will be *P* < 0.05.

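### Simple randomisation does not guarantee the stated 39 per group, and the tests stated for measurement data leave the preoperative SF-36 score unused

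*Protocol article*

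**What the plan says.** On allocation, the Randomisation and blinding section of the protocol article states: "Participants will be randomly assigned equally to the two study groups with the use of simple randomisation". On the mechanism it adds that "a third-party statistician will use computer software to generate pseudorandom numbers". It mentions no blocks, strata or fixed arm totals. The Setting section says that patients will be "divided into a treatment group and a control group, each with 39 patients", and the Methods part of the Abstract gives the same figure. The Sample size section arrives at 33 per group and, after 15% loss to follow-up, 78 in all.

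On analysis, the Secondary efficacy assessments section says: "The comparison between the groups of measurement data will be compared by the" t test or the Wilcoxon rank sum test, depending on the distribution. Count data get a chi-square or exact test, and ranked data a Wilcoxon or stratified CMH test. No covariate or stratum is named. The Recruitment and trial timeline section says of participants that "their baseline data and clinical features will be collected before the operation", and Table 1 marks the SF-36 both preoperatively and at month 6.

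**The concern.** The allocation method and the arm sizes do not fit together as written. Simple randomisation makes each assignment independently, so arm sizes are random and 39 is only their expected value. If the totals really are fixed at 39, the list is restricted and the method is not simple randomisation. A reader cannot tell which was done. At stake are accurate reporting of the allocation method and, to a small degree, power.

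The second matter is efficiency. A patient's quality of life six months after surgery is likely to be related to the level before surgery. A test on the month-6 score alone leaves that variation in the error term, although the trial already plans to collect the score that would remove it. The confidence interval for the SF-36 difference is then wider than it needs to be.

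**Working it through.** **1. Reproducing the planned size.** The Sample size section gives "the mean value of the experimental group is 10.50, the mean value of the control group is 13.40". Its SDs for these groups, in the same order, are 3.46 and 3.66, and its level is 0.05, two-sided. Power is not stated.

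- Difference: 13.40 − 10.50 = 2.90.
- Root-mean-square SD: √[(3.46² + 3.66²)/2] = √12.684 = 3.561.
- Normal approximation at 90% power: n = 2(1.960 + 1.282)² × 12.684 / 2.90² ≈ 31.7, so 32 per group.
- Unequal-variance t test (noncentral t): power 0.894 at 32 per group and 0.903 at 33. The stated 33 therefore matches 90% power. At 80% power the normal formula gives 24, which does not match.
- Dropout: 33/0.85 = 38.8, so 39 per group and 78 in total. The plan's figures reproduce.

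**2. Arm sizes under simple 1:1 randomisation of 78.** The size of one arm is Binomial(78, 0.5).

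| Quantity | Value |
|---|---|
| P(exactly 39/39) = C(78,39)/2⁷⁸ | 0.090 |
| Central 95% range for one arm | 30 to 48 |
| Mean absolute difference between arms | 7.0 patients |
| P(arms differ by 10 or more) | 0.31 |
| P(smaller arm below 33 before any dropout) | 0.14 |

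**3. Effect on power.** This uses the same difference and SDs and the unequal-variance t test. Where two values are shown, they depend on which group is the smaller.

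| Analysed | Split | Power |
|---|---|---|
| 78 | 39/39 | 0.944 |
| 78 | 34/44 | 0.939 to 0.942 |
| 78 | 30/48 | 0.928 to 0.934 |
| 78 | averaged over the binomial split | 0.941 |
| 66 | 33/33 | 0.903 |
| 66 | 28/38 | 0.892 to 0.898 |
| 66 | averaged over the binomial split | 0.898 |

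The average loss is 0.903 − 0.898 = 0.005 with 66 analysed and 0.944 − 0.941 = 0.003 with 78.

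**4. Gain from using the preoperative SF-36.** If ρ is the within-group correlation between the preoperative and month-6 scores, ANCOVA multiplies the residual variance by 1 − ρ². The article gives no ρ, so the values below are assumptions.

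| Assumed ρ | 1 − ρ² | Variance cut | Standard error cut |
|---|---|---|---|
| 0.3 | 0.91 | 9% | 5% |
| 0.5 | 0.75 | 25% | 13% |
| 0.7 | 0.51 | 49% | 29% |

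At ρ = 0.5 the gain equals that from 1/0.75 = 1.33 times as many patients for this outcome.

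**The case against.** On allocation, the word equally may mean equal probability, and 39 per group may simply be the planned size; the Sample size section itself calls 78 an expected number. The number table may also have been built with fixed totals, a detail that an article can leave to the full protocol. This is fair, and it is why the point asks only for the wording to be reconciled. It does not remove the mismatch, because the article names one method and states arm sizes that the method does not secure.

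On analysis, unadjusted tests are valid after randomisation, and covariate lists usually sit in an SAP. The article says that an SAP exists, and it is not shown. The section also opens by leaving the choice of secondary methods to the data, and the t/Wilcoxon sentence follows one about comparing general conditions, so its reach to the month-6 SF-36 can be debated. The instrument is described as homemade, so its correlation over time is unknown. All of this limits the weight of the point. What remains is that the only tests the section names for measurement data make no use of a baseline that Table 1 schedules.

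A reader might go further in several ways that the article does not support:

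- That equal arms cannot occur. They can, about 9% of the time.
- That an arm will be closed at 39, making the last allocations predictable. No section describes this, and only the clinical data manager has access to the table.
- That a 14% chance of an arm below 33 means an underpowered trial. The 33 is the requirement for equal arms; with 78 analysed, power is still at least 0.928 at 30/48.
- That all the planned tests are unadjusted. A stratified CMH test is allowed for ranked data, though without a named stratum.
- That haemorrhoid grade is a collected covariate being ignored. It appears only as an entry threshold, is not a row of Table 1, and is not shown to predict healing time.
- That continence needs a baseline-adjusted ordinal model. It is described in three categories, and no preoperative spread is given.

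**Conclusion.** The point holds in two limited parts.

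First, the allocation text and the stated arm sizes need reconciling. Under simple randomisation as written, 39/39 is a 9% event and one arm may plausibly hold anywhere from 30 to 48 patients. The cost is about half a percentage point of average power, with no bias. The power figures rest on the article's own means and SDs and on 90% power, which is inferred because it reproduces 33.

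Second, adjusting the month-6 SF-36 for its preoperative value is a better analysis than the unadjusted tests named, at almost no cost. The size of the gain depends wholly on an assumed correlation, and it arises only if the SF-36 is analysed as a score. The stated tests are inefficient, not wrong. This part concerns a secondary outcome; incision healing time and time to return to normal activities have no baseline value and are unaffected.

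**What to change.** 1. In the Abstract, Setting and Randomisation and blinding sections, describe what was actually done. If allocation is truly simple, call 39 per group the expected size. If the list has fixed totals or blocks, name that restriction and drop the word simple. This is a change of wording.

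2. Under Secondary efficacy assessments, state that the month-6 SF-36 score is compared between groups by ANCOVA with the preoperative SF-36 score as covariate, and report the adjusted difference with its 95% confidence interval. This takes one model term and no new data. Fix it before month-6 data are compared by group. If the SAP already says this, only the article needs to be brought into line.

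The article commits to submitting any modification for ethics review and to updating the registration, so both edits carry that administrative step. Switching to blocks for the remaining patients is not recommended. About two thirds are already recruited, so about 26 (78/3) would be covered. In a single-site trial with an unblinded operator and observer, blocks are also easier to predict than simple randomisation.

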#### Procedure for unblinding if needed

Participants with serious adverse events will be reported to the principal investigator and the Ethics Committee (IEC) of West China Hospital, Sichuan University, who will make the decision to unblind and withdraw them from the study.

### Intervention description

#### The treatment group

The external haemorrhoids in the mother haemorrhoid area at points 3, 7, and 11 will be removed by an ultrasonic scalpel in a V-shape;The internal haemorrhoids will be clamped with forceps to be removed, the superior haemorrhoid artery will be ligated with No. 0 mousse thread “8”, 1 ml of Xiaozhilin will be injected under the ligation proximal sticking mould, and then the haemorrhoid will be removed slowly with an ultrasonic scalpel along the clamp mark at the base;The carbonisation (fixation) range of the incision will be checked, the free carbonised tissue will be removed at the incision, a needle will be inserted at the edge of the solidified tissue to suture the incision with the figure of “8” slightly above the tooth line, and then the incision epithelium will be sutured near the tooth line with the modified “8” suture method. When there is no obvious bleeding from the wound, the operation will be considered complete.

#### The control group

The top of the external haemorrhoids will be clamped and gently pulled outwards to expose the internal haemorrhoids. A V-shaped incision will be made on the external haemorrhoids, and the subcutaneous tissue will be stripped to 0.2 cm on the tooth line. The stripped external haemorrhoids and the base of the internal haemorrhoids will be clamped with middle-curved forceps. No. 0 silk thread will be used to run through the base root of the suture clamp. Part of the internal haemorrhoid tissue will be removed without letting the suture slip off.In the same way, the other haemorrhoids will be removed and ligated, and 3 ~ 55 ml of 1:1 Xiaozhiling (1 part Xiaozhiling stock solution, 1 part normal saline) will be injected into the mucosa of the superior haemorrhoid artery area where the haemorrhoids are ligated under an anoscope to prevent bleeding. When there is no obvious bleeding from the wound, the operation will be considered complete.

### Relevant concomitant care permitted or prohibited during the trial

#### Perioperative management

After the operation, a fluid diet will be given for 1 day, and appropriate fluids will be supplemented. Nonsteroidal anti-inflammatory drugs or opioid central analgesics will be given for postoperative pain according to the VAS pain score. For postoperative urinary retention, catheterisation will be determined by the ward doctor on duty after evaluating the patient’s symptoms and signs. The patient’s catheter will be removed on POD 2. For postoperative defecation, lactulose oral solution will be used to soften the stool on the first day after the operation. If the patient still has difficulty defecating, a glycerine enema will be administered to help the patient defecate. If the symptoms still cannot be alleviated, warm normal saline can be given as a cleansing enema.

Twenty-four hours after the operation, the anal canal dressing will be removed, and the patient can defecate on their own. After defecation, the patients will be treated with heat-clearing and detoxifying traditional Chinese medicine sit-baths, iodophor disinfection, indomethacin and furazolidone embolisation of the anus, and dressing changes every day after defecation. The patient’s wound recovery, stool smoothness, and blood in the stool will be evaluated in the decision to arrange for discharge. After discharge, the patient will be advised not to exercise vigorously, continue perianal disinfection and dressing changes, and participate in regular outpatient follow-up.

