#### Secondary outcome measures

Postoperative complications: pain: A visual analogue scale (VAS) will be used in the two groups to observe the patients’ pain 4 h, 8 h, and 24 h after the operation and the pain from defecation for 7 consecutive days after the operation. Urinary retention will be assessed by the “with” and “without” method. Postoperative bleeding will be assessed as follows: 0 points: no bleeding; 1 point: blood on the paper; 2 points: drops of blood; 3 points: ejection of blood; and 4 points: massive bleeding that requires surgery to stop the bleeding. Postoperative oedema will be assessed as follows: 0 points: no oedema; 1 point: oedema in 1/4 of the anal margin incision; 2 points: oedema in 1/2 of the anal margin incision; 3 points: oedema in 3/4 of the anal margin incision; and 4 points: oedema around the perianal incision. Anal stenosis will be assessed by the “with” and “without” method.

Anal function evaluations 3 months and 6 months after operation: Anal function evaluation will be assessed by the CCF-FI as follows: (1) normal continence: the anus controls stool, and the passage of intestinal fluid and intestinal gas is normal; (2) partial anal incontinence: the anus cannot control intestinal fluid, intestinal gas, or loose stools; there is soiling of the underwear; or the anus has a sense of dampness; and (3) complete incontinence: the anus cannot control the passage of stool.

Evaluation of quality of life half a year after the operation: The simple SF-36 quality-of-life questionnaire (homemade) will be used to evaluate quality of life.

Evaluation of patient satisfaction rate half a year after the operation: The self-designed patient satisfaction questionnaire will be used, which is divided into very satisfied, satisfied, general, and no opinion, and calculates the percentages of the 4 levels.

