## Discussion

There are many surgical methods for haemorrhoids, but each has its own advantages and disadvantages. Therefore, it is particularly necessary to explore a surgical method that not only does not damage anal sphincter function but can also restore the normal shape of the anus.

The choice of surgical instruments for mixed haemorrhoids should not only take into account the different symptoms and morphological characteristics of patients with mixed haemorrhoid lesions but also local related haemodynamic changes, microcirculation control disorders, and haemorheological pathophysiological changes; the concept of “minimally invasive” should be used as much as possible to achieve a good therapeutic effect and protect the fine functions of the anus, such as defecation control. The metal head of the ultrasonic scalpel is sharp and conducive to fine anatomy and is of great value in the operation of mixed haemorrhoids. Ultrasonic scalpel haemorrhoidectomy was reported to be applied in the clinic by Jane [22] and other investigators in 2001, and research has shown that ultrasonic scalpel haemorrhoidectomy can reduce the pain and postoperative bleeding of patients. Mushaya [23] et al. conducted a meta-analysis of the comparison between ultrasonic haemorrhoidectomy and traditional haemorrhoidectomy, and the results showed that the ultrasonic scalpel group had lower pain scores, a lower complication rate, and a faster recovery than the traditional surgery group. Research by Ravi Kumar [24] et al. showed that compared with the Milligan-Morgan operation, ultrasonic haemorrhoidectomy resulted in less blood loss (19.4 and 6.1 ml, respectively). Compared with the Milligan-Morgan method group, the ultrasonic scalpel group had lower VAS pain scores on the first day and the first and the second week after the operation. There were more complications, such as postoperative bleeding and urinary retention, in the Milligan-Morgan group. In a case study of 25 patients (ultrasound scalpel group) conducted by Tariq Ahmed Mala [25], the average operation time was 17.68 ± 2.84 min, and the average operation time of the control group was 28.44 ± 3.69 min. The average blood loss of the ultrasonic scalpel group and the control group was 8.96 ± 2.15 ml and 31.72 ± 3.28 ml, respectively. VAS pain scores on the first day after surgery were 5.92 ± 0.70 in the ultrasonic scalpel group and 8.52 ± 0.84 in the control group. The ultrasound scalpel group had a lower analgesic dose, engaged in walking earlier and returned to normal work faster. In previous research reports, the vast majority of ultrasonic scalpel haemorrhoidectomy procedures were open operations only using an ultrasonic scalpel to remove the haemorrhoids; the wound was left open and drained and healed naturally. Only two studies mentioned that the incision was closed [22, 26]. Another study showed that closing the incision is not beneficial; it is not conducive to drainage of the incision and may actually slow the healing process [27]. Before the start of this study, we conducted a preliminary study: 12 patients with mixed haemorrhoids were treated with open ultrasonic scalpel resection. Unfortunately, 8 of the 12 patients had blood in the stool 5–16 days after the operation, mainly the dripping of blood and jet-like bleeding, and the amount of bleeding was ≥ 5 ml each time. Among them, 4 patients had postoperative bleeding > 50 ml. All 4 patients underwent a second haemostatic operation under anaesthesia. During the operation, the wounds were found to have ulcers and erosions and extensive bleeding after ultrasonic scalpel resection. Upon inquiry into their medical history, the 8 patients with bleeding were found to have no primary underlying diseases (hypertension, heart disease, blood system diseases, etc.) and no history of long-term anticoagulant drug use. The reasons may be as follows: if only the ultrasonic scalpel is used to remove the haemorrhoids without suturing the incision, normal defecation activity after the operation will increase the abdominal pressure and anal pressure, which will increase the tissue tension in the anal area. Under repeated stimulation from stool, the coagulated tissues will easily crack and bleed, causing incision infection and delayed healing. Therefore, we modified the open ultrasonic scalpel haemorrhoidectomy procedure. While removing the internal haemorrhoid mucosa, we sutured the base of the incision with a figure of eight and designed this research plan to evaluate its clinical efficacy and safety.

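### Analgesia is guided by the same VAS that serves as the pain outcome, and analgesic use is not compared between arms, so a VAS result cannot be attributed to the operation alone

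*Protocol article*

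**What the plan says.** Four parts of the protocol article bear on this point.

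- **Perioperative management** makes analgesia depend on the score: "Nonsteroidal anti-inflammatory drugs or opioid central analgesics will be given for postoperative pain according to the VAS pain score". The text is the same for both arms and gives no threshold. All patients also receive a daily local treatment that includes an anti-inflammatory, "indomethacin and furazolidone embolisation of the anus", which does not depend on the VAS.
- **Secondary outcome measures** uses the VAS to compare "pain 4 h, 8 h, and 24 h after the operation" and also "the pain from defecation for 7 consecutive days after the operation". Neither this list nor the primary outcome list contains analgesic use. Table 1 has a pain VAS row and no medication row.
- **Secondary efficacy assessments** leaves the analysis general ("the appropriate descriptive indicators and hypothesis testing methods will be selected") and does not mention analgesia.
- **Randomisation and blinding** says: "Since the surgical operator and the observer must know which group each subject has been assigned to, they cannot be blinded".

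The Discussion, describing an earlier comparative study, reports: "The ultrasound scalpel group had a lower analgesic dose".

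**The concern.** One instrument both prompts treatment and measures the result, over overlapping days. A patient who scores high is given a drug that lowers the next scores. If one operation hurts more, part of that difference leaves the VAS and reappears as extra analgesic use, which the plan does not compare.

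Less postoperative pain is part of the trial's rationale (Abstract and Background), and the Discussion itself treats analgesic dose as something on which the techniques can differ. Without that quantity by arm, a reader of the final report cannot tell whether similar scores mean similar operations or more drug in one arm. Nor can the reader tell whether a difference in scores comes from the operation or from different prescribing.

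**Working it through.** **Step 1: what the document supplies.** It gives the rule (VAS-guided, no threshold), the outcome (VAS over hours and days) and the unblinded staff. It gives no drug effect and no VAS standard deviation for this trial. The size of any distortion is therefore not derivable, and every input in steps 2 to 5 is an assumption made for illustration, not a suggested treatment rule.

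**Step 2: direction under an equal rule.** Let D be the difference in mean VAS without VAS-guided analgesia, r the fall in VAS produced by the drug, and pC and pT the proportions treated in the control and test arms. Then

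observed difference = D − r × (pC − pT).

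If pain is higher in the control arm and the rule is the same, pC exceeds pT and the observed difference shrinks. If pain does not differ, pC = pT and nothing is lost; the simulation with no true difference gave 0.00.

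**Step 3: illustration.** Assumed control VAS mean 6, SD 1.5, trigger at 4 or 6, r from 1 to 3, 400,000 simulated patients per arm, power at 33 per arm (two-sided 0.05):

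| True difference | Trigger | Treated, control vs test | Observed for r = 1, 2, 3 | Power for r = 1, 2, 3 |
|---|---|---|---|---|
| 1.0 | 4 | 91% vs 75% | 0.83, 0.67, 0.52 | 75%, 66%, 46% |
| 1.0 | 6 | 50% vs 25% | 0.75, 0.51, 0.26 | 74%, 55%, 18% |
| 2.6 | 4 | 91% vs 34% | 2.03, 1.46, 0.90 | 100%, 100%, 91% |
| 2.6 | 6 | 50% vs 4% | 2.13, 1.67, 1.21 | 100%, 100%, 99% |

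Without VAS-guided analgesia, power is about 77% for the 1.0-point difference and 100% for 2.6. The formula agrees with the table: 1.00 − 3 × (0.50 − 0.25) = 0.25, against 0.26 simulated. Attenuation runs from about 16%, (0.99 − 0.83)/0.99, to 74%, (1.00 − 0.26)/1.00.

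**Step 4: a second set of assumptions.** VAS 5 vs 4, SD 2, trigger at 4: 69% vs 50% are treated, and an untreated difference of 0.98 becomes 0.98 − r × 0.19 = 0.79, 0.60 or 0.41. Power at 33 per arm falls from 51% to 50%, 43% or 27%.

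**Step 5: unequal prescribing.** Take no true difference and r = 2, but let one arm be treated from a VAS of 4 and the other from 6. The arms then differ by 2 × (0.91 − 0.50) = 0.82 points, in whichever direction the prescribing goes. The simulation gave 0.82 both ways.

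**Step 6: the document's own VAS figures.** The earlier study in the Discussion reports day-1 VAS of 5.92 ± 0.70 vs 8.52 ± 0.84, a difference of 2.60, with a lower analgesic dose in the scalpel group. The pooled SD is √((0.70² + 0.84²)/2) = 0.77. If analgesia halved the difference to 1.30, the standardised distance at 33 per arm would be 1.30/(0.77 × √(2/33)) ≈ 6.8, and power would exceed 99%.

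**The case against.** The case on the other side has real force.

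- **VAS under common care is a legitimate comparison.** Both arms follow one written rule, and pain as patients experience it under that care is a valid randomised contrast. This stands. What it does not provide is the pain caused by the operation itself.
- **The article condenses a fuller protocol.** The case report form may well record medication, so the document does not show that analgesic use goes unrecorded. This stands too. The outcome list and schedule are nevertheless set out explicitly, and analgesic use is in neither.
- **A reader might infer that the VAS comparison is simply biased towards no difference.** The document does not support that. It needs a true pain difference and a rule applied equally; with unblinded staff and no stated threshold, the shift could favour either arm (step 5).
- **A reader might also infer that the pain result is likely to come out null.** Step 6 speaks against this: the only VAS figures in the document show a large difference despite unequal analgesic dose. The technique there is not identical and its analgesic rule is not given, so it does not settle the matter either.
- **The illustration is simplified.** It lowers the same reading that triggers the drug, whereas in practice only later readings change, and whether a dose still acts at a given defecation is unknown. If the dose does still act, the mean shift is the one in step 2; if not, it is smaller. Patient numbers at these early readings may also be nearer the 39 randomised per arm than 33.
- **Analgesic use is itself decided by unblinded staff.** So it is not a clean endpoint. It is still the information needed to read the VAS.

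**Conclusion.** The point holds as a limit on interpretation. VAS validly describes pain under the analgesia given, but on its own it cannot attribute a null or a positive result to the operation. The direction towards zero follows only if pain truly differs and the rule is applied equally; otherwise the sign is open. No size can be taken from the document. The range of about 16% to 74% attenuation, and the 0.8-point shift under unequal prescribing, rest wholly on assumed thresholds, drug effects and SDs. Pain is a secondary outcome, and incision healing time and return to normal activities are not affected. This is a cheap improvement, not a defect that threatens the trial.

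**What to change.** Leave analgesic care unchanged. In Secondary outcome measures, add in-hospital analgesic use from the drug chart, compared between arms: any opioid (yes/no), and total analgesic doses to discharge or day 7. State that VAS is reported alongside it, and that neither a null nor a positive VAS result is attributed to the operation without it. For patients still to be enrolled, also record whether analgesia preceded each VAS reading. This timing may not be recoverable for the roughly two thirds already recruited according to Trial status.

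The cost is chart abstraction for 78 patients, one more secondary outcome, and the ethics submission and registry update that the section on protocol amendments requires.
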